### Study Population and Sample Size

The trial will include 130 adults aged 18 to 60 years with opioid use disorder who are already receiving buprenorphine treatment, with no criteria regarding gender identity, race, or ethnicity.

Inclusion criteria are having the ability to provide informed consent, age 18 to 60 years, having adequate English proficiency, being within the first 120 days of starting buprenorphine, receiving buprenorphine pharmacotherapy under the care of a licensed health care provider and being willing to provide the name of the provider or practice, being capable of using common software apps on a smartphone, and having access to an internet-enabled smartphone that meets minimal operating system requirements for the duration of the study. Exclusion criteria are having a history of reSET-O use, having participated in user-testing of PEAR-008 or any investigational drug trials within 30 days of trial enrollment, or currently receiving methadone or naltrexone pharmacotherapy.

The sample size and power were based on the primary engagement outcome, determined by frequency of interaction with the intervention, percentage of module completion, and approval ratings. A sample size of 130, α=.05, and power=0.80 will allow for detection of a moderate effect size (*d*=0.50).

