### Randomization and Blinding

Following informed consent, the baseline assessment and confirmation of eligibility, participants will be randomly assigned to 1 of 2 treatment groups: reSET-O or PEAR-008. Randomization lists will be prepared by the study sponsor (Pear Therapeutics) prior to the start of the study. Randomization will be 1:1 and stratified by site and gender with a block size of 10. An electronic list of IDs, access codes, and credentials will be securely provided to the sites. There will be no blinding; this is an open-label study.

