### Endpoints

#### Primary Endpoint Analysis

Engagement with PEAR-008 and reSET-O will be defined as the number of active sessions per week. A session is defined as a set of in-app events with the same session ID. An active session is any session that contains some active participation in the app such as navigating to a different screen, engaging with a learning module, or responding to a notification. This endpoint was selected to allow a 1:1 comparison of content delivery method (eg, brief chapters vs longer lessons). The number of active sessions per week will be evaluated with a repeated measures mixed model of the form: *Number of Sessions in a Week = Week + Treatment + Week × Treatment + Subject Error + Random Error*. To evaluate the impact of treatment, this repeated measures mixed model will be compared to another of the form: *Number of Sessions in a Week = Week + Subject Error + Random Error* with a likelihood ratio test. The likelihood ratio test will be evaluated using model fit to maximize the log-likelihood.

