#### Secondary Endpoint Analysis

Abstinence will be self-reported by patients via timeline followback and assessed as the absence of opioids (except buprenorphine) on saliva drug screens. Data on abstinence (binary yes and no) will be evaluated with the 9 possible saliva drug screens and urine drug screen and timeline followback data at weeks 1-8 and week 12. Differences between the treatment arms in abstinence will be assessed with a generalized estimating equation analysis using the binomial abstinence outcome as the dependent variable, assessment time, treatment, and the interaction between assessment time and treatment as fixed effects and subject as a random factor. This generalized estimating equation will be compared to a second generalized estimating equation without a treatment term using a likelihood ratio test to evaluate the impact of treatment. A treatment responder analysis will also be conducted, with a treatment responder defined as someone with ≥80% of all saliva drug screens and urine drug screens and timeline followback reports negative for all nonprescribed opioids over the course of the trial.

Treatment retention will be measured as time to dropout (number of days from baseline to last face to face contact) and analyzed using the Kaplan Meier method followed by a log rank test to compare treatment groups.

Patient assessments of recovery capital (Brief Assessment of Recovery Capital–10) resilience (Connor-Davidson Resilience Scale–10) and severity of co-occurring psychiatric symptoms (Patient Health Questionnaire–8 and Generalized Anxiety Disorder Questionnaire–7) will be evaluated with a repeated measures mixed model in a manner consistent with the primary endpoint.

Participants’ use patterns with PEAR-008 and reSET-O will include total time engaged, number of lessons and chapters completed, number of lessons and chapters repeated, number of completed self-report assessments, and response to notifications. Descriptive statistics of each treatment arm will be summarized and differences between PEAR-008 and reSET-O will be assessed with a *t* test (or its nonparametric alternative if the distributional assumptions are violated).

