#### Exploratory Endpoint Analysis

Data on abstinence (binary—yes and no) will be evaluated at 9 saliva drug screen and timeline followback time points at weeks 1-8 and week 12. The association between abstinence and engagement will be evaluated using a generalized estimating equation model. A given week will be considered negative if a participant has no indication of opioid use on the saliva drug screens or timeline followback. Missing data will be ignored if saliva drug screens or a timeline followback is available for a given time point. In the case where saliva drug screens and timeline followback methods yield data that do not agree, the week will be considered positive.

The relationship between engagement and retention will be assessed using a Cox proportional hazards model with time to dropout as the dependent variable and the number of active sessions as an independent variable. This analysis will be performed separately for each treatment arm.

Patient assessment of skill acquisition (Cognitive Behavioral Therapy Skills Questionnaire) will be evaluated with repeated measures mixed model analysis consistent with the primary endpoint. Results will be presented for the total Cognitive Behavioral Therapy Skills Questionnaire score, the Behavioral Activation Score, and the Cognitive Restructuring score.

Medication adherence will be evaluated using saliva drug screens and, when possible, confirmed by urine drug screen (positive result for buprenorphine and norbuprenorphine). Differences between the treatment arms in medication adherence will be assessed with a generalized estimating equation analysis consistent with the abstinence analysis.

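### With only a subject error and a random error, the primary likelihood ratio test can exceed its 5% level, substantially if week is linear

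*Protocol article*

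**What the plan says.** Primary Endpoint Analysis writes out two models for weekly active sessions. The full model is "Number of Sessions in a Week = Week + Treatment + Week × Treatment + Subject Error + Random Error" and the reduced model is "Number of Sessions in a Week = Week + Subject Error + Random Error". Treatment is judged by comparing the two: "The likelihood ratio test will be evaluated using model fit to maximize the log-likelihood". The section mentions no random slope, serial correlation, unstructured covariance or robust variance, and it does not say whether Week is a linear trend or a 12-level factor.

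The same approach is carried further. In Secondary Endpoint Analysis, the recovery capital, resilience, depression and anxiety scales "will be evaluated with a repeated measures mixed model in a manner consistent with the primary endpoint". In Exploratory Endpoint Analysis, the skills questionnaire "will be evaluated with repeated measures mixed model analysis consistent with the primary endpoint".

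**The concern.** A subject error plus a random error, read in the usual way, means that every pair of weeks is equally correlated and that all participants in an arm share one time trend. Weekly app use is unlikely to behave like that. The article itself treats dropout as an outcome and plans to relate it to active sessions. reSET-O has a finite set of 67 lessons, and PEAR-008 rewards daily use. Different rates of decline and persistence from week to week are therefore to be expected.

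The planned test removes Treatment and Week × Treatment together. Under compound symmetry the interaction is compared with week-to-week residual noise. If participants have their own slopes, the relevant noise is the variation of slopes between people, which the model leaves out. A model-based likelihood ratio has nothing to correct for this. At stake is the level of the only primary test: two apps with identical engagement could be declared different more often than the stated α of .05.

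**Working it through.** **Inputs from the article.** 130 participants, 1:1, so 65 per arm; α=.05; 12 weeks, taken as 12 weekly counts per participant; the two models above. **Assumed, because the article gives none:** all variances and correlations, and complete data.

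**1. The plan's own figure.** Two-sided comparison of two means: n per arm = 2(1.960+0.842)²/0.50² = 62.8, so 63 (126 in total). The t-test version needs 64 per arm (128), and 65 per arm gives power 0.808. So "A sample size of 130, α=.05, and power=0.80 will allow for detection of a moderate effect size" reproduces. It contains no repeated-measures covariance and is not in dispute.

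**2. Degrees of freedom.** Linear week: 1 (Treatment) + 1 (interaction) = 2. Categorical week: 1 + 11 = 12.

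**3. Closed form, linear week.** For weeks 1–12, Sxx = 12(12²−1)/12 = 143. Take residual variance σ² = 4 (SD 2) and participant slopes with SD τ, independent of the participant's mean level.

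- True variance of a participant's fitted slope: σ²/Sxx + τ².
- Variance the planned model uses: (σ² + τ²·143/11)/143 = (4 + 13τ²)/143.
- r = true/model. Under no arm difference the test statistic behaves as A + rB, where A and B are independent chi-squares on 1 df, referred to 5.991. A is the comparison of participant means and keeps its correct distribution. Only B is distorted.

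| τ (sessions/week per week) | true | model | r | size |
|---|---|---|---|---|
| 0 | 0.0280 | 0.0280 | 1.00 | 5.0% |
| 0.1 | 0.0380 | 0.0289 | 1.31 | 7.6% |
| 0.2 | 0.0680 | 0.0316 | 2.15 | 14.9% |
| 0.3 | 0.1180 | 0.0362 | 3.26 | 23.4% |

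For AR(1) residuals with correlation matrix R, centred weeks t and centring matrix P, r = [t′Rt/143²] / [tr(PR)/(11·143)]. This gives r = 1.67, 2.42 and 3.62 for ρ = 0.3, 0.5 and 0.7, and sizes 10.7%, 17.2% and 25.7%. For ρ = −0.3, r = 0.60 and the size is 2.6%.

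**4. Simulation of the planned test, no arm difference** (4,000–10,000 trials per row; the likelihood ratio formula was checked against a mixed-model fit):

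| Truth | Linear, 2 df | Categorical, 12 df |
|---|---|---|
| Compound symmetry | 4.9% | 5.4% |
| Slope SD 0.1 / 0.2 / 0.3 (intercept SD 3, residual SD 2) | 8.2 / 14.9 / 23.9% | 6.1 / 6.4 / 8.1% |
| Slope SD 0.02 / 0.05 / 0.10 total-SD units (intraclass correlation 0.5) | 5.8 / 10.0 / 23.6% | 4.9 / 5.2 / 8.0% |
| AR(1) 0.3 / 0.5 / 0.7 (intraclass correlation 0.5) | 10.7 / 17.4 / 25.7% | 6.2 / 8.4 / 10.6% |
| AR(1) −0.3 (intraclass correlation 0.5) | 2.5% | 5.9% |
| 6% stop per week, zeros afterwards | 12.9% | 6.0% |
| Overdispersed counts, log-slope SD 0.10 | 22.2% | 7.4% |

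At intraclass correlation 0.3, AR(1) 0.7 gave 27.5% and 10.7%. The most extreme count scenario tried (log-slope SD 0.15) gave 31.8% and 11.6%.

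**5. Size of the alternatives.**

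- t test on participants' 12-week means: 4.5–5.4% in every scenario tried.
- Joint 2-df test on participant mean and slope: 4.3–5.6% with an exact F reference, 4.7–6.0% with the chi-square likelihood ratio.
- Categorical week, unstructured covariance: 3.9–5.2% with an exact F reference, but about 6–8% with the plain chi-square likelihood ratio, even when compound symmetry is true.
- Categorical week, participant-clustered robust Wald test (identity link) without small-sample correction: 10.5–11.1%.

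**The case against.** Four points can be made for the plan.

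- **Independence is inferred.** The article gives a general form and never says the random error is independent across weeks. An unseen analysis plan could give the residual a structure. This stands as a caution on wording. It does not remove the point, because the article goes beyond naming a mixed model: it writes out an equation with two error terms, and adding a random slope would depart from it.
- **The large rates need linear week.** This stands. With categorical week the excess is modest, and some of it is a small-sample effect of the 12-df chi-square reference (5.4% with the model correct). But the coding is not stated, so the serious case remains open.
- **Not every departure inflates the test.** A reader might infer that any difference in trends or any correlation between weeks breaks the 5% level. The calculations do not support that. Slope SD 0.02 or 0.05 with categorical week gives 4.9% and 5.2%, and negative serial correlation with linear week is conservative.
- **Some obvious repairs do worse.** An unstructured covariance with the plain chi-square test, or an uncorrected robust Wald test, can have a higher false-positive rate than the planned test when week is categorical. This stands and shapes the fix.

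**Conclusion.** The point holds in limited form. The primary test as written can exceed 5% when usage trends differ materially or neighbouring weeks are positively correlated. Under the assumed variances the rate is about 8–27% with linear week and about 5–11% with categorical week; one extreme count scenario went somewhat beyond both. The closed form and the simulation agree for linear week.

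These are ranges under assumptions. The article supplies no covariance figures, so no single rate can be attributed to this trial. The excess comes from the Week × Treatment part, and with complete data the arm comparison of mean weekly sessions remains sound. A reader might conclude that the whole engagement comparison is invalid or that 130 is the wrong sample size; neither follows. The scales share the model but are measured only at baseline and weeks 4, 8 and 12, and the excess there has not been quantified.

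**What to change.** Keep the endpoint. State how week is coded and replace the error structure, with the same covariance in the full and reduced models.

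- **Linear week:** add a participant random slope, with serial correlation if needed, or test each participant's mean and slope jointly with an F reference.
- **Categorical week:** use an unstructured covariance with a small-sample F reference (for example Kenward-Roger), not the plain chi-square likelihood ratio test.
- **If a participant-clustered robust Wald test is preferred:** give it a small-sample correction.

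Make the same change for the scales analysed in line with the primary endpoint. The cost is analysis-plan wording, a few lines of code and a slightly less favourable p-value. No new data are needed.

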**Primary**			
	To evaluate participant engagement with PEAR-008 compared to that with reSET-O. The hypothesis is that PEAR-008 group will have significantly greater participant engagement than the reSET-O group.	Number of active sessions with PEAR-008 or reSET-O per week	

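### The primary likelihood ratio test pools treatment level and time course, so a significant result does not establish greater engagement, and the stated 80% power was not shown for it

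*Protocol article*

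**What the plan says.** The hypothesis in Table 1 is directional: "The hypothesis is that PEAR-008 group will have significantly greater participant engagement than the reSET-O group". The Methods paragraph of the Abstract says the same. The endpoint is the number of active sessions per week.

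The Primary Endpoint Analysis section writes out two models. The full one contains week, treatment, week-by-treatment, a subject error and a random error. The section continues: "To evaluate the impact of treatment, this repeated measures mixed model will be compared to another of the form", and gives the reduced model as "Number of Sessions in a Week = Week + Subject Error + Random Error". The two are compared by a likelihood ratio test on maximum likelihood fits, and this comparison is the stated means of judging the impact of treatment. The section does not say whether week is linear or categorical. It names no single treatment contrast as the basis of the primary conclusion.

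The Study Population and Sample Size section says: "A sample size of 130, α=.05, and power=0.80 will allow for detection of a moderate effect size", with d=0.50. It bases the calculation on a primary engagement outcome "determined by frequency of interaction with the intervention, percentage of module completion, and approval ratings".

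**The concern.** Removing treatment and its interaction with week in one step makes the test ask whether the arms differ in any way over the 12 weeks, in level or in shape. The hypothesis asks something narrower: whether engagement is greater with PEAR-008.

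Two things are at stake. First, the primary p-value can be small when average engagement is the same in both arms and only the pattern over time differs. A fading novelty effect is plausible here, because PEAR-008 is built as a game that rewards daily use. Second, a constant average gain is spread over more degrees of freedom than the sample-size statement appears to assume, so the stated power may belong to a different test. The sample-size text also describes an outcome other than active sessions per week, which loosens the link further.

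**Working it through.** **Inputs from the protocol article.** N=130, alpha .05, power 0.80 and d=0.50 (Study Population and Sample Size); 1:1 allocation, so 65 per arm (Randomization and Blinding); 12 weeks (Abstract, Methods); the two models (Primary Endpoint Analysis).

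**Assumptions, because the article does not give them.** Two-sided test; normal outcome; complete data; the same correlation ρ between any two weeks of one participant, as a subject error plus a random error implies; for the power figures, a treatment effect constant over weeks.

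**Step 1: degrees of freedom.** With linear week, the full model has one treatment and one interaction parameter beyond the reduced model: 1 + 1 = 2. With categorical week over 12 weeks: 1 + 11 = 12.

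**Step 2: reproduce the stated figure.** A two-sided two-sample t test with 65 per arm and d=0.50 has power 0.808; the normal approximation gives 0.813. The t test needs 64 per arm, 128 in all, for 80%. A one-sided test would have 0.886. The stated figure is therefore most naturally a two-sided 1-df comparison of two means.

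**Step 3: the planned test, with d on the participant's 12-week mean.** The noncentrality is λ = (N/4) × d² = 32.5 × 0.25 = 8.125. Power is the probability that a noncentral chi-square with this λ exceeds the 5% critical value.

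| Test | Critical value | Power at λ=8.125 | N for 80% | Detectable d at N=130 |
|---|---|---|---|---|
| 1 df | 3.84 | 0.813 | 126 | 0.49 |
| 2 df | 5.99 | 0.725 | 156 | 0.55 |
| 12 df | 21.03 | 0.408 | 278 | 0.73 |

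Simulating the maximum likelihood test in a balanced random-intercept model (4,000 runs per case) gave 0.71 to 0.72 at 2 df and about 0.40 at 12 df.

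**Step 4: the same test, with d on a single week's SD.** The variance of a 12-week mean is the weekly variance times ρ + (1−ρ)/12, so λ = 8.125 / (ρ + (1−ρ)/12).

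| ρ | λ | 1 df | 2 df | 12 df |
|---|---|---|---|---|
| 0.3 | 22.67 | 1.00 | 0.99 | 0.91 |
| 0.5 | 15.00 | 0.97 | 0.94 | 0.72 |
| 0.7 | 11.21 | 0.92 | 0.86 | 0.56 |
| 0.9 | 8.94 | 0.85 | 0.77 | 0.45 |

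For 80% power λ must reach 9.64 (2 df) or 17.34 (12 df). Setting ρ + (1−ρ)/12 equal to 8.125/9.64 = 0.843 gives ρ = 0.83. Setting it equal to 8.125/17.34 = 0.469 gives ρ = 0.42. Above those correlations the joint test falls below 80%.

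**Step 5: equal averages, different shape.** Let the difference between arms run linearly from +0.25 to −0.25 weekly SD over the 12 weeks, so that the 12-week means are equal. The squared weekly differences sum to 0.0625 × 572/121 = 0.2955, and λ = 32.5 × 0.2955 / (1−ρ) = 9.60 / (1−ρ).

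| ρ | λ | Rejection, 2 df | Rejection, 12 df |
|---|---|---|---|
| 0.3 | 13.7 | 0.92 | 0.67 |
| 0.5 | 19.2 | 0.98 | 0.85 |
| 0.7 | 32.0 | 1.00 | 0.98 |

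In a simulation of a wider crossing (±0.3 weekly SD, ρ=0.6), the joint test rejected in 0.999 (2 df) and 0.989 (12 df) of runs. A 1-df treatment test rejected in 0.047, its nominal level.

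**The case against.** The strongest defence is that a joint test can suit this trial. The Objective asks how participants interact with the new format, and the Conclusions ask whether the format affects use, so a change in time profile is relevant. The article also states no rule by which a significant test counts as success. This stands as a reason to keep the interaction in the analysis. It does not make the joint test a test of greater average engagement, which is the hypothesis that the article attaches to the primary endpoint.

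Three stronger readings are tempting, and the document does not support them.

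- **That the planned test lacks 80% power.** The article fixes neither the SD behind d=0.50 nor the coding of week. On the single-week reading, the joint test exceeds 80% over a wide range of correlations, especially with linear week. For the same reason, the 1-df match is the most natural source of the stated figures but not the only possible one. The figure of 0.41 needs both categorical week and d on participant means.
- **That the likelihood ratio p-value is too small, because app-use counts will not fit a random intercept with constant residual variance.** The model formula is schematic. The residual covariance, count distribution and robust errors are commonly left to an analysis plan, which is not shown. Any size for the inflation would rest on assumed count parameters that the article does not give.
- **That the fault is rejection in either direction.** A two-sided 1-df test also rejects when reSET-O is better. The difference is that a single contrast has a sign and an interval, so its rejection can be read as greater or lesser engagement. The Hedges g in the Statistical Analysis section is a general summary measure and is not tied to the primary test.

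**Conclusion.** The point holds in this form: the primary test is joint, with 2 or 12 df, and its rejection alone does not establish greater engagement. With equal 12-week means and a crossing of ±0.25 weekly SD, it would reject in 92 to 100% (2 df) or 67 to 98% (12 df) of trials for correlations of 0.3 to 0.7. This follows from the two models as written. The crossing pattern and the correlations are illustrations.

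The stated power matches a two-sided 1-df comparison and was not shown for the planned test. Whether the planned test falls short is conditional. On participant means, power is about 0.72 or 0.41. On a single week's SD, it is 0.86 to 0.99 (2 df) or 0.56 to 0.91 (12 df) for correlations from 0.7 down to 0.3. All power figures assume a constant effect, normal outcomes and complete data; dropout would lower them.

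The mismatch between the outcome in the sample-size text and the primary endpoint needs no assumption, since the two descriptions differ on the page.

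**What to change.** 1. Make the primary test the 1-df treatment contrast: the difference between arms in mean weekly active sessions averaged over weeks 1 to 12, two-sided at 5%, reported with its 95% confidence interval.
2. Keep week-by-treatment in the analysis as a secondary description of how the difference changes over time, and state how week is coded.
3. Rewrite the sample-size sentence to name active sessions per week as the outcome, the 1-df test as the basis of the power, and the SD on which d=0.50 is defined.

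With d on the 12-week mean, the existing 130 participants give this contrast power of 0.81, so no extra recruitment is needed. The cost is wording in the protocol and analysis plan, settled before the data are analysed. The small downside is that the primary test becomes less sensitive to an effect that changes only the time profile.
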